infant breast milk intake, gut inflammation, multivariable linear regression models will be used. Covariates identified as potential confounders will be included in the regression models for adjustment. Regression analysis will also be done to examine the effect of infant milk intake, postpartum depressive symptoms and gut inflammation on linear growth velocity (birth to 3 months and 3 to 6 months) and LAZ scores of the LBW infants. To assess dose-response relationships between duration of KMC and volume of breast milk output generalized additive models shall be used. We may also use Instrumental Variable analyses to study associations between actual intensity of SSC and Breast feeding and the outcomes of the proposed studies.

For qualitative outcomes e.g. mothers with PHQ9 score  $\geq 10$ , lactation failure, perceived milk insufficiency, proportions will be reported. If necessary to adjust for any baseline differences, univariable and multivariable logistic regression analysis or analyses with generalized linear models of the binomial family with a log link shall be done to estimate the impact of KMC on these outcomes. Potential interaction between cKMC and all other variables on the outcome measures will be examined by including interaction terms in the multivariable regression models, after identifying subgroup differences by simple stratified analyses. In order to quantify biologic interactions(52) we will estimate the relative excess risk due to interaction(RERI) with its 95% CI(53, 54).

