## **4.2 Disadvantages**

*Specify the physical, psychological, social and/or practical risks/harm/discomfort/strain/inconvenience, now or in the future, for the individual patients/participants, groups of people, society and/or the environment.*

The visits from our workers took up to 3 hours each time so a few women became tired but none were fatigued. There were several visits in the home but less than 10 women, most of them in the control arm of the trial, seemed inconvenienced by our interaction with them. All women were comfortable after the team explained the importance and relevance of our examinations.

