## Methods

### **Brief description of the main trial** (in which this research will be embedded)

To answer the objectives of this research, a sub-study will be embedded in the large ongoing individually randomized controlled trial entitled “*Impact of Community-initiated Kangaroo Mother Care on Survival of Low Birth Weight Infants*” ([www.clinicaltrials.gov](https://www.clinicaltrials.gov/ct2/show/study?term=NCT02653534&rank=1) #NCT02653534) where 10,500 LBW infants will be enrolled to examine the impact of community initiated KMC on neonatal and infant mortality(6).The identification, screening and enrolment of mother-infant dyads for this sub-study will be embedded within the main trial.

*Setting:* The trial is being conducted in the rural and semi-urban areas of districts of Faridabad and Palwal in the state of Haryana (India), with a population of ~2 million, annual birth rate of 25.6/1000 population with around 20% of the babies being born with LBW.

*Population:* The study population comprises of mother infant dyads with babies weighing  $\geq 1500$  g to  $\leq 2250$  g enrolled within 3 days of birth identified by the study surveillance teams, either born at home or discharged from hospital and for whom KMC was not initiated in the hospital.

*Inclusion and exclusion criteria:* Infants unable to feed, with breathing problems, major congenital malformations or less active on the day of visit are referred to hospitals. Those intending to move away over the next 6 months or refuse participation are also excluded.

*Screening, enrolment and randomization:* In the main trial, pregnant women are being identified and followed up, their babies are weighed at birth and enrolled if eligible by study workers. Additionally, infants who are ill or whose weight is  $< 1800$ g are counseled to visit health facilities as mandated by government. However contact is maintained with such families and they are screened for enrolment when discharged from hospital if still within the 3 day enrolment window. Eligible infants are randomized using a randomization list prepared by an offsite statistician from WHO not otherwise involved with the trial. Allocation of subject IDs is done using serially numbered opaque sealed envelopes. At baseline, following consent, a questionnaire is administered to obtain sociodemographic details and child anthropometry is done.

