*Intervention:* The intervention group will receive KMC, i.e. promotion of and support for SSC and EBF as soon as possible after birth by study Auxiliary Nurse Midwives (ANMs) supported by study Accredited Social Health Activists (ASHAs) in addition to the routine postnatal visits by government health workers. The study visits are made daily for the first 3 days, on days 5 and 7,

twice in the second week and once each in weeks 3 and 4. Study ANMs and ASHAs visit together on the first 3 days. Visits will continue till 28 days or till the baby wriggles out. Information on the duration of SSC per day and number of breastfeeds over the last 24 hours will be captured. For any illness, referral will be facilitated through government ASHAs. The babies in the control arm of the trial receive routine postnatal visits by government health workers as implemented through the health system.

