### **Description of the PhD sub-study**

*Sample sizes for the sub-study (Vide Annexure 3):*

With 95% confidence and 90% power and expecting approximately 10% attrition, a total sample size of:

- 550 mother-infant dyads (275 in each group), will be sufficient to detect a 0.3 SD, i.e. 60ml, increase in infant breast milk intake with 90% power (1SD = 200ml),
- 1950 mother-infant dyads (975 in each group) will be sufficient to detect a 30% relative reduction in the prevalence of moderate to severe postpartum depressive symptoms (PHQ 9  $\geq 10$ ), assuming a baseline prevalence of 19%,
- 550 mothers will be sufficient to detect a 0.3 SD i.e. 1.5 ug/dl decrease in the mean saliva cortisol levels (biomarker of stress),
- 250 infants (125 in each group) will be sufficient to detect a 0.5 SD reduction in the levels of gut inflammatory markers.

Therefore, the overall sample size will be 1950 mother infant dyads in whom the prevalence of postpartum depressive symptoms will be assessed using PHQ 9. Infant breast milk intake, and salivary cortisol (biomarker of stress) will be assessed in a sub-sample of 550 subjects; Infant gut inflammatory markers will be assessed in 250 subjects. Information on the linear growth-related outcomes and possible serious bacterial infection will be available for all these study subjects. The secondary outcomes related to breastfeeding i.e. lactation failure, perceived milk insufficiency, breastfeeding performance will be measured in the sub-sample of 550 subjects.

*Inclusion and Exclusion:* Singleton Low birth weight babies ( $\geq 1500$  to  $\leq 2250$  g) aged  $>72$  hours to 7 days who are either born at home or hospital but KMC not initiated in the hospital and are already a part of the trial titled “Effect of Community Initiated Kangaroo mother care on babies with Low Birth Weight” will be included in this sub-study.

In the sub-study, we will exclude infants whose mother expired or is not living with the baby for any reason. Also for the subsample of the 550 mothers where infant breast milk intake will be assessed, twins or triplets (~5% of the total LBW births) will be excluded because of the difficulties involved in accurately assessing breast milk output in mothers with twins/ triplets using the deuterium oxide method.

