*Enrolment in the sub-study and collection of baseline data:* Out of all the LBW infants enrolled in the main trial, a sub-sample of the LBW infants aged >72 hours to 7 days and their mothers will be included in this sub-study. Among the subjects enrolled in the main trial in a day, 4-6 subjects will be selected randomly per day and approached by the supervisor on Day 4 for obtaining additional consent for the sub-study. In case of non-consent, the subsequent mother-infant dyad will be approached. Data will be recorded to keep track of mothers who consented and did not provide consent. In these women, additional samples or information will be collected for the sub-study. Baseline information will be collected for the sub-study to describe the study sample and to adjust for any confounding. These variables include sociodemographic details (age, years of schooling of the mother, wealth index, total family income, family type, religion and working status of mother), reported gestational age, birth order, place and mode of delivery, birth weight of the baby, previous breastfeeding experience, maternal dietary habits, iron and calcium tablet intake, history of maternal post-partum illnesses (fever). Maternal anthropometry (height and weight) will also be done at enrolment to ascertain baseline nutritional status.

*Informed Consent:* Written individual informed consent for this sub-study will be obtained from the caregivers at enrolment, from whom additional samples and information will be collected. The informed consent form for the sub-study has been translated into simple Hindi language that can be easily read and understood. The purpose of the study, procedures to be performed, samples to be collected and stored will be explained in detail. In those who are unable to read, the worker who obtains consent will read out the consent form. The mothers' understanding of the information will be confirmed. In those who are unable to sign, a thumb imprint will be taken which will be witnessed (counter signed) by an impartial literate witness. Only the eligible LBW babies, whose parents provide informed consent will be enrolled for this study.

*Outcome ascertainment:* Outcomes specific to the sub-study will be measured by a independent team trained in the study related measurements and laboratory procedures in the study subjects enrolled through home visitations. There will be a total of 4-5 such teams. Each team comprises

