**Plan of Analysis**

The analysis will be done using STATA version 14 (Stata Corporation, College Station, TX). All analysis will be performed on intent to treat basis.

Group wise comparison will be done for distribution of baseline features such as

- household characteristics (wealth quintile, religion, caste, type of family, number of family members)
- maternal and paternal characteristics (mother's age, mother's education, maternal occupation, father's age, father's education and occupation)
- birth related characteristics (place and type of delivery, birth order, parity) and
- infant characteristics (sex, birth weight, gestational age)

Proportion who initiated breastfeeding within 1 hour, exclusive breastfeeding, hospitalizations (at the 1 month visit) will also be presented by group.

Gestational age will be calculated from ultrasonography (USG) report, hospital records or maternal recall, whichever available, in the given order of preference. Proportion of women with available antenatal USG will be reported.

The distribution of the continuous outcomes such as (maternal salivary cortisol concentration, PHQ-9 scores) will be examined by using histogram and normal probability plot. Skewness and kurtosis coefficient will be measured. If skewness coefficient tends to zero and kurtosis coefficient tends to 3, distribution will be normal. For normal distribution, mean and standard deviation (SD) will be reported for quantitative variables. Median and interquartile range (IQR) will be reported for non-normal distribution. For non-normal continuous outcomes appropriate transformation (log or others) will be done before applying the tests of association or we will use non-parametric tests such as Wilcoxon rank-sum test will be performed for comparison between study arms.

The proportion of minimal, mild and moderate to severe depressive symptoms as defined by the PHQ-9 scores will be presented by group.

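### Sub-study entry is settled on days 4-7, after allocation, by a second consent with replacement of refusers, so the analyses labelled intention-to-treat do not compare the randomised groups

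*Combined protocol and SAP*

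**What the plan says.** **Randomisation.** The protocol's description of the main trial has dyads "enrolled within 3 days of birth identified by the study surveillance teams", and at that point "Eligible infants are randomized using a randomization list prepared by an offsite statistician from WHO".

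**Contact before sub-study entry.** In the intervention arm, "The study visits are made daily for the first 3 days, on days 5 and 7". Control families get only the routine government postnatal visits.

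**Sub-study entry.** The section describing the PhD sub-study takes infants older than 72 hours and up to 7 days. Of each day's main-trial enrolments, 4-6 dyads are drawn at random and a supervisor asks for additional consent on Day 4. Then: "In case of non-consent, the subsequent mother-infant dyad will be approached". Consents and refusals are recorded. There is also an eligibility condition: "In the sub-study, we will exclude infants whose mother expired or is not living with the baby for any reason".

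**Analysis.** The protocol's data analysis paragraph claims intention-to-treat. The SAP's Plan of Analysis says: "All analysis will be performed on intent to treat basis". Neither defines the set of subjects. The SAP's sample size section says that 1950 mothers were enrolled, 975 per group, and does not mention the Day 4 draw, the second consent or replacement. The only remedy offered is regression adjustment for variables whose distribution differs between the groups by more than 10% in relative terms.

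**The concern.** The random draw of 4-6 dyads is harmless. The second consent after it is not protected by randomisation. The intervention is behavioural, so by Day 4 most families will know which care they are receiving. A mother's willingness to join may then depend on her arm, and her mood may also affect it. The SAP's primary outcome is PHQ-9 of 10 or more, so refusal that depends on arm and mood together distorts the comparison directly.

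Extra refusal by affected control mothers would hide a real benefit. Extra refusal by affected KMC mothers would create a false one. Adjustment for measured characteristics that differ among those who joined does not address selection on mood, and no mood measure is scheduled before day 28. The consent log could show whether the arms differ in refusal, but no planned analysis uses it.

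**Working it through.** **1. The plan's own figure.** Inputs from Annexure 3: 0.19 against 0.133, 90% power, 5% alpha. Two-sided testing is assumed, since it is stated only for the gut markers.

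n = [1.96·√(2·0.1615·0.8385) + 1.2816·√(0.19·0.81 + 0.133·0.867)]² / 0.057² = 874 per arm, as stated. Allowing 10% attrition, 874/0.9 gives 972 against the planned 975. The sample size is sound; the issue is who is analysed. Below, n = 877 per arm (975 less 10%), where power is 90%.

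**2. Model for selective consent.** With true prevalence p, and consent c_d among mothers who would score 10 or more and c_n among the others, the prevalence seen among participants is

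p_obs = p·c_d / [p·c_d + (1 − p)·c_n].

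All consent and refusal rates below are assumptions. Power and type I error use the two-proportion normal approximation with pooled variance under the null.

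**3. True ratio 0.70, mood affects consent in the control arm only.** KMC prevalence stays at 0.133.

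| Control consent, affected / other | Observed control prevalence | Apparent ratio | Power |
|---|---|---|---|
| 88% / 90% | 0.1672/0.8962 = 0.187 | 0.71 | about 87% |
| 85% / 90% | 0.1615/0.8905 = 0.181 | 0.73 | about 80% |
| 80% / 90% | 0.1520/0.8810 = 0.173 | 0.77 | about 63% |

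**4. No true effect (0.19 in both arms), affected KMC mothers refuse 10 points more often.**

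| Base refusal | Observed KMC prevalence | Apparent ratio | Type I error |
|---|---|---|---|
| 5% | 0.1615/0.9310 = 0.173 | 0.91 | 15% |
| 10% | 0.1520/0.8810 = 0.173 | 0.91 | 16% |
| 20% | 0.1330/0.7810 = 0.170 | 0.90 | 19% |

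Overall refusal in that arm rises by only 0.19 × 10 = 1.9 points, so similar overall refusal rates would not rule the bias out.

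**5. Mood affects consent equally in both arms (80% / 90%).** Control 0.173, KMC 0.1064/0.8867 = 0.120, ratio 0.70, power about 88%. The bias is about nil: distortion needs refusal to depend on arm and mood together.

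**The case against.** Extra procedures need extra consent, and analysing consenting participants by allocated arm is often called intention-to-treat. Refusals are logged. Field staff who handle dyads are not given the objectives or full protocol, and a separate team measures outcomes. The model also ties consent on Day 4 to PHQ-9 status on day 28, so a given gap on the later outcome requires a larger gap on mood at the time of consent. These points are fair and limit the likely size. They do not make the analysed groups the randomised ones.

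Several stronger readings are tempting, and the documents do not support them:

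- *Refusers were replaced within arm until each quota was full, which hid differential refusal.* The protocol says only that the next dyad is approached. Without arm matching, differential refusal would show as unequal counts.
- *Staff seeking consent knew the arm.* This is not stated. Blinding is stated only for laboratory personnel, so families' awareness is a fair inference but the supervisor's is not established.
- *The exclusion of mothers not living with the baby is a selection that KMC affects.* The ethics application, section 3.1, lists the same criterion as a general exclusion at screening. Only a change between randomisation and days 4-7 would count, and nothing shows that this is common or depends on arm.
- *Section 4.2 of the application shows that controls refused more.* It reports that "less than 10 women, most of them in the control arm of the trial, seemed inconvenienced by our interaction with them". These women were already receiving visits, and the section says that all were comfortable after explanation. This is not refusal data.
- *The effect could be reversed.* In the cases calculated, a true 0.70 crosses 1 only with 30 points of extra refusal among affected controls on a base refusal of 20% (0.0950/0.7430 = 0.128; 0.133/0.128 = 1.04).

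**Conclusion.** The concern holds in a limited form. The plan claims a property that its analysis set does not have: the comparison is by allocated arm among those who, after allocation and up to 3 days of KMC visits, were still eligible and consented. Covariate adjustment as planned does not address refusal that depends on arm and mood.

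The possible size is material. Gaps of 5-10 points confined to the control arm cost about 10 to 27 points of power, and a 10-point gap confined to the KMC arm roughly triples the type I error. Both results rest on assumed consent rates, since the documents give none. The direction is open, and under equal mood effects the bias almost vanishes. A reader might infer that the trial's result is biased, but the documents show only how it could be. This should be corrected because the remedy is inexpensive and the data for it are already part of the trial.

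**What to change.** Change the SAP only:

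1. Replace the intention-to-treat label with *analysed as randomised among selected and consenting sub-study participants*.
2. Report by arm, using the consent log, the numbers randomised, selected, ineligible (with infant death and mother-infant separation shown), refused, replaced and assessed. State whether replacement was within arm and whether the person seeking consent knew the allocation.
3. Compare refusers with participants within each arm on main-trial baseline data (sociodemographic details and infant anthropometry).
4. For PHQ-9 of 10 or more, pre-specify two sensitivity analyses beside the main result. One is an inverse-probability-of-participation weighted estimate, with weights from those baseline data. The other is a bounds or tipping-point analysis that varies the prevalence among refusers separately by arm.
5. State that weighting corrects only for measured variables. Do not make agreement between weighted and unweighted results a condition for the conclusion: if refusal is driven by unmeasured mood, both can be biased alike.

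No change to the exclusion for mothers not living with the baby is needed; the SAP reports enrolment in the past tense. The cost is a small amount of extra analysis and a slightly less precise weighted estimate. Sample size is unchanged.

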## **Outcomes**

### **Primary**

1. Infant breast milk intake during the neonatal period
2. Moderate to severe maternal postpartum depressive symptoms (Patient Health Questionnaire-9 score  $\geq 10$ ) and salivary cortisol levels at the end of neonatal period
3. Gut inflammatory markers: Fecal Neopterin, Myeloperoxidase,  $\alpha 1$ -antitrypsin at baseline and at the end of neonatal period

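### The sub-study's adjustment rules admit covariates measured after randomisation, which KMC visits may already have changed; limit adjustment to pre-randomisation variables

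*Combined protocol and SAP*

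**What the plan says.** **Randomisation and intervention.** Under the protocol's description of the main trial, dyads are "enrolled within 3 days of birth identified by the study surveillance teams", and "Eligible infants are randomized using a randomization list prepared by an offsite statistician". At that enrolment, "At baseline, following consent, a questionnaire is administered to obtain sociodemographic details and child anthropometry is done". KMC support is meant to begin promptly after birth: "The study visits are made daily for the first 3 days, on days 5 and 7", with further visits to week 4.

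**Sub-study enrolment.** The sub-study samples infants already in the main trial, at more than 72 hours to 7 days of age, with the approach on day 4. There, "Baseline information will be collected for the sub-study to describe the study sample and to adjust for any confounding". The list runs from sociodemographic items, gestational age, birth order, delivery and birth weight to "maternal dietary habits, iron and calcium tablet intake, history of maternal post-partum illnesses (fever". Maternal height and weight are measured at the same enrolment.

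**Stool.** The first sample is requested on the day of sub-study enrolment, with up to 3 working days allowed to obtain it. The primary outcome lists the gut markers "at baseline and at the end of neonatal period". The matching primary objective refers only to levels at the end of the neonatal period.

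**Adjustment rules.** The protocol's data analysis section puts covariates identified as potential confounders into multivariable models and does not name them. The SAP's plan of analysis, which covers depressive symptoms and cortisol only, adds any variable whose relative difference between arms exceeds 10%.

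**The concern.** A covariate measured after allocation is safe to adjust for only if allocation cannot have changed it. For the variables recorded at the sub-study visit that can still move, the plan gives no such assurance. The SAP's imbalance rule makes this sharper: if KMC visits shift a variable, the shift appears as an imbalance between arms, and the imbalance is what brings the variable into the model. The adjusted coefficient would then no longer estimate the total effect of KMC.

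The first stool sample raises a related question of labelling. It is called baseline but is taken after randomisation, and its role in the analysis is not stated. Anyone who treats it as a true baseline might adjust for it or subtract it.

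**Working it through.** **1. Order of events**

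| Event | Timing | Protocol section |
|---|---|---|
| Main-trial enrolment and randomisation | within 3 days of birth | Brief description of the main trial |
| First KMC visits | daily for 3 days, then days 5 and 7 | same, Intervention |
| Sub-study enrolment and covariates | >72 hours to 7 days | Enrolment in the sub-study |
| First stool | from sub-study enrolment, up to 3 working days later | Outcome ascertainment |

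The sub-study visit always follows randomisation and, in the KMC arm, normally follows some visits. How much exposure precedes it varies. If main-trial enrolment is near 72 hours and the sub-study visit is on day 4, it may be about a day; with early enrolment and a day-7 visit, it may be most of a week. The protocol does not say whether the first 3 days are counted from birth or from enrolment.

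**2. Which covariates can move**

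- Fixed before randomisation: maternal age, schooling, religion, gestational age, birth order, place and mode of delivery, birth weight, previous breastfeeding experience. Recording these late does no harm.
- Able to change after randomisation: maternal diet, iron and calcium intake, post-partum fever, maternal weight.

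**3. What adjustment would do**

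In a linear model, let δ be the change that KMC has already caused in a covariate and γ that covariate's coefficient for the outcome, given arm. Then

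adjusted effect = total effect − γ × δ.

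If δ = 0, this term vanishes. If not, the sign depends on both quantities. The documents give neither, so no figure can be attached to diet, supplements, fever or weight.

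**4. The stool marker, as an illustration only**

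The plan's own sample size reproduces. For 0.5 SD, two-sided 5% and 90% power, n per arm = 2 × ((1.960 + 1.282)/0.5)² = 84.06, against the stated 84. With 125 per arm less 10% attrition, about 112 remain, and power for 0.5 SD is Φ(0.5 × √56 − 1.96) = Φ(1.78) = 96.3%.

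Suppose the early marker were used as a covariate. Assume KMC has already lowered it by d₀ SD and that it correlates ρ with the day-28 value within arm; neither value is in the documents. The adjusted effect is 0.5 − ρ × d₀:

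- d₀ = 0: 0.50 SD, no loss.
- d₀ = 0.1, ρ = 0.2: 0.48 SD.
- d₀ = 0.25, ρ = 0.5: 0.375 SD (simulation 0.374, against 0.499 unadjusted).
- d₀ = 0.3, ρ = 0.7: 0.29 SD.

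The main cost is bias rather than power, because adjustment also shrinks the residual SD. In the third case it is √(1 − 0.25) = 0.866, the standardised effect is 0.375/0.866 = 0.433, and power at 112 per arm is Φ(0.433 × √56 − 1.96) = Φ(1.28), about 90%. Allowing for the correlation between arm and early marker gives 89.5%.

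A change score would remove all of d₀. In the same case it leaves 0.25 SD, with SD √(2 × 0.5) = 1 and power of 46.4% at 112 per arm. No section plans either analysis.

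**The case against.** **Unadjusted comparisons are planned.** The protocol lists unpaired t-tests or Mann-Whitney tests by arm, and the SAP runs univariable models first. This stands: the randomised contrast is available and unaffected. A reader might infer that the sub-study baseline breaks the randomised comparison; it does not. But the protocol gives multivariable regression as the means of estimating effects on quantitative outcomes, the SAP treats the univariable model as a first step, and neither says which result is primary.

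**The SAP's list of baseline features contains none of the four variables.** True, and this lowers the risk for PHQ-9 and cortisol. The list is introduced as examples, however, and the 10% rule is not confined to it. The SAP also tabulates exclusive breastfeeding and hospitalisation at the 1-month visit by arm, and nothing bars those from the model.

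**No effect of KMC on the four variables is documented.** The intervention promotes skin-to-skin contact and breastfeeding, with no stated maternal diet or supplement component. This stands, and it is why the bias is described as possible rather than shown.

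**No stool-adjusted or change-score analysis is planned.** This also stands. The objective, the hypothesis on mean values, the planned tests by arm and the sample size based on a difference between groups all point to a comparison of end-of-period levels.

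**Consent after allocation.** Dyads are approached on day 4, and "In case of non-consent, the subsequent mother-infant dyad will be approached". A reader might infer selection bias in every sub-study outcome. Selection for approach is random, consents and refusals are logged, and the documents show no difference in refusal by arm. A count by arm would be useful; the documents do not establish a bias.

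**Conclusion.** The point holds as a gap in the adjustment rules. Four variables that can change after randomisation are recorded at the sub-study visit; three are in the list collected partly for adjustment, and maternal weight is measured alongside them. Neither selection rule keeps them out. If KMC has shifted one of them and it predicts the outcome, the adjusted estimate is biased by an amount and in a direction that the documents do not allow one to calculate. Covariates fixed before randomisation carry no such risk, and required sample sizes are unchanged.

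A reader might count days (4/28 = 14% to 7/28 = 25%) or visits (3/9 = 33% to 5/9 = 56%) before the sub-study visit and take those as the share of the gut-marker effect lost. The documents do not support this: it assumes KMC from birth, an effect that builds up in proportion to time or visits, and a change-score analysis that is not planned. The stool figures above rest on assumed values of d₀ and ρ and show only what an unstated analysis could do.

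**What to change.** 1. In the protocol's data analysis section and the SAP's plan of analysis, restrict adjustment to named variables that are fixed before randomisation or recorded at main-trial enrolment. Remove maternal diet, iron and calcium intake, post-partum fever and maternal weight at day 4-7 from the adjustment set; they can still be reported descriptively. Apply the same limit to the 10% imbalance rule.
2. State that the primary gut-marker analysis compares day-28 levels by arm, as the objective and the planned tests already imply. In the list of primary outcomes, relabel the enrolment stool as an early post-randomisation measure that is neither a covariate nor a change-score reference in that analysis.
3. Optionally, tabulate sub-study consent and refusal by arm from the existing log. No weighted analysis is required.

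The cost is a few lines of text. No new data are needed, and the only loss is any precision that the early stool value would have brought.
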